### Dropout and withdrawal

2.8

Participants may withdraw voluntarily at any point or be removed by the investigator, with the main reason recorded. Those exiting before treatment begins count as screening failures and, barring medical need, need not complete discontinuation evaluations. Withdrawals due to adverse events (AEs) will receive suitable care, and monitoring will persist for intervention-related AEs until resolved or stabilized. Exclusion criteria include: (1) participant or legal representative requesting withdrawal or revoking consent; (2) newly identified conditions impacting study results; (3) major breaches of inclusion/exclusion rules; (4) confirmed pregnancy; (5) a serious AE necessitating withdrawal or making involvement impractical; (6) barriers to conducting medical or traditional Korean medicine (TKM) procedures for lumbar disc herniation; (7) investigator judgment that ongoing participation is unsuitable; or (8) herbal medicine adherence below 70% across 5 weeks or fewer than six usual care sessions attended. Follow-up assessments may proceed with consent after treatment ends.

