	Anthropometric measurements	●												●			
	Concomitant medication review^8^	●	●					●				●		●	●	●	●
	Adverse effect assessment^9^			●		●		●		●		●		●	●	●	●
Treatment compliance assessment^10^				▲^11^		▲^11^		▲^11^		▲^11^		▲^11^		▲^11^			
Experimental group^11^			■		■ (10D)			■ (20D)									
Control group^12^				▲	▲	▲	▲	▲	▲	▲	▲	▲	▲				

1 Follow-up visits at weeks 12, 19, and 26 may be conducted via telephone surveys if in-person visits are impractical. In such cases, vital signs and VAS measurements were omitted.

2 Missing follow-up questionnaires (including telephone surveys) due to a participant’s missed visit will not be considered a protocol violation.

3 For the experimental group, weeks −1 and 0 visits were conducted on the same day. For the control group, weeks −1, 0, and 1–1 visits can were conducted on the same day.

4 Lumbar spine CT or MRI examination results, whether performed at the current institution or other hospitals, may be used if previously acquired.

5 At week 3, the assessment of the NRS, VAS, ODI, EQ-5D-5L, HINT-8, GPE, healthcare utilization costs/time survey, time–cost evaluation, productivity loss, and vital signs may have been conducted concurrently with the day 20 visit for the intervention group. For the control group, these assessments will be performed at week 3–1, or week 3–2 if not completed at week 3–1.

6 NRS, ODI assessments, and medical cost surveys at week 5 will be conducted via telephone survey.

7 Participants will undergo blood and urine tests at weeks −1 and 7. They would be required to visit after an 8-h fasting period on the day prior to blood collection for the tests. Retesting for abnormal results may be performed at the discretion of the investigator. However, for week −1 clinical laboratory tests, the results from tests conducted within 14 days of the screening visit can be substituted. The specific test items were as follows: (a) blood test items: WBC, RBC, neutrophils, lymphocytes, monocytes, eosinophils, basophils, MCV, MCH, MCHC, hemoglobin, hematocrit, platelet count, total protein, albumin, ALT, AST, ALP, total bilirubin, gamma GT, uric acid, BUN, creatinine, BUN/creatinine ratio, serum glucose, PT, aPTT, ESR, and CRP. (b) Urine Test Items: specific gravity, pH, protein, glucose, ketones, urobilinogen, bilirubin, blood, nitrite, WBC (leukocytes). For female participants, urine HCG screening was performed at week −1.

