8 During the concomitant medication review, both the dosage and frequency of use will be investigated.

9 For the herbal medicine strategy group, adverse events will be confirmed via weekly phone calls starting from week 1 after herbal medicine administration. For TKM treatment group, these assessments were conducted at weeks 1–2, 2–1, 3–1, 4–1, and 5–1. If not conducted during the first visit of the respective week from week 2 to 5, it may be conducted during the second visit of that week.

10 For treatment compliance verification, in the herbal medicine strategy group, the number of days herbal medicine was not taken since receipt was assessed weekly from weeks 1 to 5. At week 7, the total number of prescribed herbal medicine packs and the number of remaining packs were recorded in the CRF. For TKM treatment group, the total number of administered treatments will be recorded in the CRF at week 7.

11 Participants in the herbal medicine strategy group will visit weeks 0, day 10, and day 20 to receive and take a 10-day supply of herbal medicine, totaling 30 days.

12 The frequency of usual TKM treatment will generally adhere to a standard of twice per week but may be adjusted to 1–3 times per week based on the clinician’s judgment regarding the patient’s symptoms, with the total number of sessions not exceeding 10.

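### Investigators may remove treated participants for low adherence or on judgment, and nothing then secures their week-7 NRS and ODI for the ITT analysis

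*Protocol article*

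**What the plan says.** Section 2.8 (Dropout and withdrawal) allows the investigator to take participants out of the trial. Besides withdrawn consent and pregnancy, the listed grounds are a newly found condition (2), an eligibility breach (3), a serious adverse event (5), obstacles to carrying out procedures (6), investigator judgment (7) and ground 8: "herbal medicine adherence below 70% across 5 weeks or fewer than six usual care sessions attended". People who leave before treatment are handled separately, as screening failures who "need not complete discontinuation evaluations" unless medically required. The numbered grounds therefore reach people already randomised and treated. On data collection afterwards the section says only "Follow-up assessments may proceed with consent after treatment ends".

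Section 2.7 makes ITT (at least one dose or session) the primary set and per-protocol (at least 70% herbal compliance, or at least 7 sessions) supportive.

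The notes to Table 1 also bear on this:

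- Note 12: control treatment is normally twice weekly but "may be adjusted to 1–3 times per week based on the" clinician's judgment, up to 10 sessions.
- Note 10: in the herbal arm "the number of days herbal medicine was not taken since receipt was assessed weekly from weeks 1 to 5"; in the control arm "the total number of administered treatments will be recorded in the CRF at week 7".
- Note 1: "Follow-up visits at weeks 12, 19, and 26 may be conducted via telephone surveys if in-person visits are impractical". Week 7 is not listed.
- Note 2: a follow-up questionnaire that is missing because of a participant's "missed visit will not be considered a protocol violation". Its marker is on the Follow-up heading, which covers the week-7 column.

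**The concern.** Stopping treatment and leaving the study are treated as nearly the same event. Someone who takes too little medicine, attends too few sessions, or is judged unsuitable by a clinician who knows the allocation can be removed, and week-7 NRS and ODI are then optional. These people remain in the ITT set by definition, but their primary outcomes can be missing for reasons tied to behaviour or unblinded judgment after randomisation. Missing at random is then doubtful.

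Because ground 8 largely selects the same people that the per-protocol rule excludes, losing their outcomes brings the observed ITT data closer to the per-protocol data. Agreement between the two analyses would then be weaker reassurance than it appears. The Background relies on intention-to-treat principles to safeguard internal validity, and the Discussion cites the ITT and per-protocol analyses as mitigating bias. The Background also promises sensitivity tests for adherence and treatment frequency, which need outcomes from exactly these patients.

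**Working it through.** **1. Removal rule against per-protocol rule**

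| Arm | Removal, ground 8 (2.8) | Per-protocol (2.7) | Relation |
|---|---|---|---|
| Herbal | below 70% | 70% or more | exact complement |
| Control | fewer than 6 sessions | 7 or more sessions | complement except at 6 sessions |

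**2. Removal rule against permitted treatment.** The lowest permitted frequency in note 12 gives 1 session × 5 weeks = 5 sessions, and 5 < 6. A control patient treated as allowed meets a removal ground.

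**3. Can ground 8 act before week 7?** Herbal treatment lasts 30 days, and 70% of 30 is 21 days. If adherence is counted in days, a patient with more than 9 missed days is already below 70%, and missed days are checked weekly in weeks 1 to 5. Control treatment is planned over 5 weeks, so the session count is known by about week 5. Removal before the week-7 visit is therefore possible, although no text says that the weekly checks trigger it.

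**4. The plan's allowance for loss.** Table 2 goes from 33 to 37 per arm: 33 / 0.90 = 36.7, rounded up to 37, which reproduces with its 10% dropout. That allows 37 − 33 = 4 losses per arm (10.8%) from all causes. Removal of 15% alone would be 0.15 × 37 = 5.55, or 5 to 6 per arm. The text of Section 2.3 anticipates 15% attrition, but the enrolment figure allows only for the 10%.

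**5. Size of a possible bias (illustration).** Assumptions not in the documents:

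- Proportions removed without follow-up, p_h (herbal) and p_c (control), each take the values 0.05, 0.15 or 0.25.
- Removed patients improve D = 5 or 10 ODI points less than those retained.
- The correlation between visits is 0.6, with compound symmetry.

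A completers' mean overstates an arm's improvement by p × D, so the between-arm shift is (p_h − p_c) × D. The extreme differences in proportions are ±0.20, giving ±1.0 (D = 5) or ±2.0 (D = 10). The shift is 0 when the arms lose equal proportions.

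A repeated-measures mixed model uses the week-3 and week-5 values. Let a and b be the shares of the week-7 shortfall already visible at weeks 3 and 5. The weight on each visit is 0.6 / (1 + 0.6) = 0.375, so the fraction of bias left is 1 − 0.375 × (a + b). With week 3 only, the weight is 0.6.

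| Case | Fraction left | D = 5 | D = 10 |
|---|---|---|---|
| Completers only | 1 | ±1.0 | ±2.0 |
| a = b = 1 | 1 − 0.375 × 2 = 0.25 | ±0.25 | ±0.5 |
| a = 0.5, b = 0.8 | 1 − 0.375 × 1.3 = 0.51 | ±0.51 | ±1.0 |
| Week 5 also missing, a = 0.5 | 1 − 0.6 × 0.5 = 0.70 | ±0.70 | ±1.4 |

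The yardstick is the 5-point difference in Section 2.3. That section does not name the scale. I take it as ODI, because an SD of 10 cannot belong to a 0–10 scale.

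**The case against.** The strongest reply is that this is a condensed article. Only those who leave before treatment are excused from discontinuation evaluations, so such evaluations evidently exist for treated participants, and the full protocol may specify them. The permissive sentence can even be read as a safeguard, since it keeps follow-up open after treatment stops. This stands in part: loss is possible, not certain. But the article does not say that those evaluations include NRS or ODI or fall at week 7, and the finding rests on a stated permission beside stated removal grounds, not on silence alone.

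Timing is the second reply. Ground 8 is assessed over five weeks and final counts are recorded at week 7, so it need not act before the primary visit, and the week-3 and week-5 measurements would usually already be due. This also stands in part. The case with week 5 missing fits the other grounds, or an unusually early use of ground 8, better than routine use of ground 8. Those other grounds have no per-protocol counterpart in Section 2.7, so for them the issue is selective loss, not drift toward per-protocol.

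Third, note 2 classifies a missed questionnaire and does not cancel it, and week 7 has a +14-day window. Both are true, but neither requires collection after removal.

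Finally, the five-session case needs once-weekly treatment throughout, and the magnitudes are assumed. The widest case needs a 20-percentage-point imbalance and a shortfall twice the design difference. The illustration also leaves out NRS and the LOCF handling named in Section 2.7.5.

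**Conclusion.** The point holds. As written, Section 2.8 allows selective loss of week-7 primary outcomes from the ITT set in both arms, through grounds that depend on adherence or on unblinded judgment. Its control-arm threshold also conflicts with the minimum treatment frequency the protocol permits.

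Whether bias follows, and in which direction, cannot be known in advance. Under the stated assumptions it runs from zero (equal removal) to about ±0.5 to ±1.4 ODI points after mixed-model analysis in the widest case, or 10% to 28% of the 5-point difference (0.5 / 5 and 1.4 / 5). Confidence is high about the rule and low about the size of its effect. It should be fixed now: recruitment is under way, and week-7 data not collected cannot be recovered by later analysis.

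**What to change.** Amend Section 2.8 to separate stopping study treatment from withdrawing consent to data collection:

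1. State that grounds 2, 3 and 5 to 8 end study treatment at most.
2. State that week-7 and later scheduled outcomes will be collected for every randomised participant unless consent to data collection is withdrawn.
3. Extend the telephone option in Table 1 note 1 to NRS and ODI at week 7, as note 6 already does at week 5.
4. Use the adherence criterion in ground 8 only to define the per-protocol set. This also removes the conflict with once-weekly control treatment.

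The cost is one amended paragraph, one table note and a few extra contacts within visits and calls already scheduled.

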### Safety

2.9

The investigator will evaluate and document all adverse events (AEs) and serious adverse events (SAEs) during the study, adhering to WHO intensity classification guidelines, with non-covered AEs graded as: grade 1 (mild, transient, no treatment or activity limitation); grade 2 (moderate, mild to moderate activity limitation, may require treatment and recovery); or grade 3 (severe, marked limitation, requiring medical intervention or hospitalization). AEs and SAEs will be recorded in the Case Report Form (CRF) using medical terminology or detailed symptoms/signs, with pre-existing conditions noted in screening history and pre-treatment AEs documented separately. Emergency responses include oral NSAIDs for sudden pain exacerbation and immediate cessation, first aid, and emergency referral for acupuncture-related AEs (e.g., pneumothorax, bleeding, fainting). SAEs, except minor gastrointestinal discomfort (e.g., heartburn from herbal medicine), will be reported to the principal investigator or coordinator per regulations within 30 days post-trial. The CRF AE log will capture symptoms, onset, intensity, course, actions, outcome, and causality, with ongoing AEs reviewed, resolved AEs updated, escalating AEs logged anew, and treatment adjustments documented.

### Data management

2.10

Quality control (QC) and data management protocols will safeguard the accuracy, integrity, and confidentiality of trial data. Secure, password-protected electronic Case Report Forms (eCRFs) within a validated electronic data capture (EDC) system—equipped with range checks and logical constraints—will facilitate data collection while reducing entry errors. All research staff will receive standardized training in study protocols, data acquisition, and QC procedures. Source data verification (SDV) will encompass 100% of primary endpoint data and 10% of secondary endpoint data to confirm alignment with original records. Data will reside on a secure, firewalled server featuring nightly automated backups, with access restricted to authorized individuals through a rigorous control matrix that permits read-only privileges for analysts and full privileges solely for the principal investigator and data manager.

## Discussion

3

LIDH presents a complex clinical challenge, driving significant patient preference for diverse treatment modalities, including TKM (28). Despite this established patient inclination, robust clinical evidence, particularly from PRCTs, remains crucial for objectively validating the effectiveness and safety of individual TKM interventions for LIDH (29). This study outlines a PRCT specifically designed to assess the comparative benefits of incorporating herbal medicines into a comprehensive TKM treatment strategy for LIDH-related LBP and radiculopathy.

The selection of a PRCT design is a deliberate choice that acknowledges the inherent complexities and individualized nature of TKM. Unlike explanatory trials that prioritize internal validity under tightly controlled conditions, PRCTs aim to maximize external validity by reflecting real-world clinical practice (30). This design enabled assessment of the interventions’ overall effectiveness—a critical metric in TKM, where regimens adapt dynamically to individual symptoms and progress. By contrasting a herbal medicine-inclusive group with a standard TKM cohort (herbal medicine excluded), the study precisely measures herbal contributions within real-world TKM practice. Clinician discretion in modality selection, guided by expertise, enhances the results’ generalizability and relevance to routine care.

This trial addresses a notable gap in the existing literature by directly comparing herbal medicine strategies with other established TKM interventions. While previous studies have explored various TKM modalities for LBP, including acupuncture (31) and pharmacopuncture (32), and some PRCTs have contrasted TKM with conventional medicine, comprehensive PRCT focusing on the strategic role of herbal medicine in LIDH are scarce. A comprehensive suite of patient-reported outcomes—encompassing pain intensity, functional disability, quality of life, and global perceived effects—coupled with rigorous safety monitoring and cost-effectiveness assessments, generated robust evidence. These data inform clinical decisions, refine patient management, and may underpin evidence-based guidelines for integrated care of lumbar intervertebral disc herniation (LIDH). The predefined statistical plan, which handled missing data and pragmatic design features, bolstered the credibility and clarity of results, advancing insight into herbal medicine’s contribution to LIDH treatment.

Nevertheless, limitations persist. Enrolling patients with disc pathology of “bulging or worse” captured real-world TKM presentations of neurocompressive radiculopathy and axial pain yet compromised cohort uniformity, potentially attenuating effect-size precision and complicating interpretation across severity strata. Subgroup analyses stratified by radiological grade will temper this concern and strengthen applicability to routine practice. The open-label format, inevitable in pragmatic research, invited performance and detection biases from treatment awareness; furthermore, the modest sample (*n* = 74), powered for superiority, constrained non-inferiority exploration. Blinded outcome assessment, intention-to-treat, and per-protocol analyses mitigated these risks, though larger trials incorporating placebo arms remain warranted. Finally, absence of fixed treatment algorithms fostered clinical variability, risking dilution of intervention-specific signals and internal validity. Subsequent investigations should enforce protocol standardization, mandate granular documentation of therapeutic rationales, and deploy techniques such as propensity score matching to sharpen causal inference and broaden generalizability.

## Ethics approval and consent to participate

4

This study adheres to ethical guidelines to ensure voluntary participation and protect vulnerable populations, defined as those susceptible to undue influence (e.g., medical/pharmacy students, healthcare workers, pharmaceutical employees, military personnel) or with limited autonomy (e.g., individuals with incurable diseases, institutionalized, unemployed, impoverished, ethnic minorities, homeless, refugees, minors, or unable to provide informed consent). Special protections are afforded to these groups, and participation by clinical research institution employees is confirmed as voluntary through handwritten statements. Given the prevalence of lumbar intervertebral disc herniation in older adults (≥70 years), the exclusion criterion of inability to provide written informed consent is strictly enforced. Participants unable to read consent materials will have them read by an impartial third-party witness, and investigators will explain the consent form clearly and slowly to ensure informed, voluntary participation.

The study protocol received ethical approval from multiple Institutional Review Boards (IRBs) at Kyung Hee University Hospital in Gangdong (IRB No. KHNMCOH 2024–05-001, 25 September 2024), Dongguk University Bundang Oriental Medicine Hospital (IRB No. 2024–006, 4 November 2024), and Jaseng Hospital of Korean Medicine (IRB No. JASENG202410005-HE001, 20 November 2024), and Bucheon Jaseng Hospital of Korean Medicine (IRB No. JASENG202410004001-HE001, 20 November 2024). This protocol is officially registered with the Clinical Research Information Service (CRIS) of the Korea Disease Control and Prevention Agency (KDCA), National Institute of Health, under registration number KCT0010035 (Registration date: 25 September 2024).
